#### Single-item anxiety and depression scores

The cCBT system asks patients to rate two questions at the beginning of their session every time they log-into the cCBT system (8 times). These are: ‘How anxious or stressed have you felt in the past week?’ where 0 represents not at all and 8 represents extremely anxious), and ‘How depressed have you felt in the past week?’ where 0 represents not at all and 8 represents extremely depressed,.

#### Suicide

The cCBT system automatically asks questions about the presence & frequency of suicide thoughts and about suicide intent at the beginning of each session every time patients log-into the cCBT system (8 times). Patients answer the following questions: ‘Have you had any thoughts about suicide in the last week?’ (yes/no). If yes, ‘How often have you thought about ending your life in the last week?’ (once, twice, three times, more than three times), and ‘How seriously have you planned to carry it out?’ (0, not very seriously; 8, very seriously).

#### Individual problem scores

The patient describes up to three problems during their first cCBT session every time they log in to the cCBT system at the beginning of their session (8 times) and then they rate the level of distress that each problem causes for them (0, no distress; 8, extreme distress).

#### Patient experiences

#### Computer-patient alliance scale (C-PAS) and therapist-patient alliance scale (T-PAS)

These are two 15-item questionnaires that measure patients’ experiences of using computerised self-help and of having individualised support. Each item asks the patient to rate the statement that best describes their experience with either cCBT or with the support they received, on a 9-point scale, where 0 represents ‘not at all’, and 8 represents ‘extremely’). The two scales are matched item-by-item to allow comparisons of the same therapeutic elements between using a computer vs. speaking to a person (for example, ‘The therapist has contributed to improving my problems.’ vs. ‘The computer system has contributed to improving my problems.’).

These are bespoke scales developed by the Chief Investigator (LG) to assess therapy processes and patient experiences in relation to this study. Existing standardised measures, such as the Agnew relationship measure
[46] or the working alliance inventory
[47], are designed for conventional face-to-face psychotherapy and include many items that are not relevant or did not address the objectives of this study.

#### Patient experience interview (PEI)

The interview follows a structured guide with specific questions and prompts under four headings: a) general experiences and perspectives of treatment; b) hindering, unhelpful, negative or disappointing aspects of treatment; c) productive, helpful, positive or encouraging aspects of treatment; d) suggestions and additional comments.

#### cCBT system usefulness, relevance and ease of use

The cCBT system automatically asks three questions at the end of each cCBT session (8 times) about patient experiences of using the system. These are; ‘Looking at session x: How useful was it?’ (on a scale of 0 to 8, where 0 represents not at all useful, and 8 represents very useful); ‘Was it relevant to your problems? (on a scale of 0 to 8, where 0 represents not at all relevant, and 8 represents very relevant) and ‘How easy was it to follow?’ (on a scale of 0 to 8, where 0 represents very difficult, and 8 represents very easy).

#### Resource use

#### Resource use questionnaire (RUQ)

The RUO is a standardised measure developed for this project to estimate which resources and services patients have been using in relation to their depression before, during and after cCBT. The questionnaire has 10 sections that elicit information about patient contact with healthcare professionals, use of other agencies and services, medication and help from friends and family.

#### Therapist session records

Support staff maintain detailed electronic records of the content of their sessions with individual patients and their actual duration using a stop-watch; these are kept in a password-protected web-based database at the UEA. A random selection of the support sessions is taped each time with the patient’s agreement. This is to ensure session fidelity to the study protocol and to allow for qualitative comparisons in the style and content of support between the clinician and the assistant. The support staff also keep written records of the duration and content of their supervision sessions with the study’s clinical supervisor (NR).

### Sample size

Sample size calculations are based on a between-group comparison of post-treatment scores at 12-weeks follow-up post-randomisation on our primary outcome measure (WSAS), assuming a significance level of 0.05 with a standard deviation of 8.5 for that measure; this standard deviation was taken from Proudfoot *et al*.
[6], whose study used the same intervention, outcome measure and follow-up interval.

A sample size of 35 per group (total 140 patients) is sufficient to detect main effects (brief vs. extended, and clinician vs. assistant) of 0.477 standard deviations (about 4.1 points) in our primary outcome measure with 80% power, or of 0.522 (about 4.4 points) in our primary outcome measures with 90% power. The estimated sample size of 140 patients with available data can detect an interaction effect (for example, the difference between brief and enhanced, compared between clinician and assistant) of about 0.961 standard deviations (about 8.2 points) on our primary outcome measure with 80% power.

Allowing for a 30% drop-out rate, we intend to randomise 50 patients in each of the four groups (total 200 randomised patients). We estimate that about a third of all screened patients may be unsuitable for the trial or refuse participation (based on a similar pragmatic trial by Marks *et al*.
[48]), therefore to achieve 200 randomised patients we aim to recruit a total of 300 referrals.

Our sample size calculation and effect estimates are conservative. Our hope is that adjustment by the corresponding baseline outcome measure reduces the standard error of the effect estimates and hence increases the power for a given sample size.

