**Methods/design:**

This is a two-by-two factorial RCT investigating the effectiveness, cost-effectiveness and acceptability of cCBT supplemented with 12 weekly phone support sessions are either brief (5–10 min) or extended (20–30 min) and are offered by either an expert clinician or an assistant with no clinical training. Adults with non-suicidal depression in primary care can self-refer into the study by completing and posting to the research team a standardised questionnaire. Following an assessment interview, eligible referrals have access to an 8-session cCBT programme called *Beating the Blues* and are randomised to one of four types of support: brief-assistant, extended-assistant, brief-clinician or extended-clinician.

A sample size of 35 per group (total 140) is sufficient to detect a moderate effect size with 90% power on our primary outcome measure (Work and Social Adjustment Scale); assuming a 30% attrition rate, 200 patients will be randomised. Secondary outcome measures include the Beck Depression and Anxiety Inventories and the PHQ-9 and GAD-7. Data on clinical outcomes, treatment usage and patient experiences are collected in three ways: by post via self-report questionnaires at week 0 (randomisation) and at weeks 12 and 24 post-randomisation; electronically by the cCBT system every time patients log-in; by phone during assessments, support sessions and exit interviews.

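### The main effect stated as detectable with 90% power (0.522 SD, about 4.4 points) should be 0.552 SD (about 4.7 points); at 0.522 SD the power is about 87%

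*Protocol article*

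**What the plan says.** The Sample size section of the protocol article bases the calculation on WSAS scores at 12 weeks, "assuming a significance level of 0.05 with a standard deviation of 8.5 for that measure". It does not say whether the test is one- or two-sided. It gives two detectable main effects for 35 analysed patients per cell (140 in total): 0.477 SD, about 4.1 points, with 80% power; and a second "of 0.522 (about 4.4 points) in our primary outcome measures with 90% power". Drop-out of 30% is handled separately, by randomising 200 to retain 140.

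The section ends by saying "Our sample size calculation and effect estimates are conservative", and gives as its reason the hope that adjusting for the baseline score will shrink the standard error.

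The abstract quotes only the higher power level: the sample is "sufficient to detect a moderate effect size with 90% power" on the WSAS. It attaches no number to the effect.

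**The concern.** The 80% and 90% figures describe the same design, so they should differ only through the power term. They lie too close together for that: 0.522 is only 9% above 0.477, whereas moving from 80% to 90% power at two-sided 0.05 raises the detectable effect by about 16%. At least one of the two must be wrong.

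The points value does not expose the error, because it was computed from the same number: 0.522 × 8.5 = 4.44. A reader who checks SD units against points finds them in agreement. The statement concerns the primary outcome, and 90% is the power level carried into the abstract. A reader weighing a null main effect would therefore credit the design with slightly more power than its stated calculation gives.

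**Working it through.** **Inputs, all from the Sample size section.** Analysed patients: 35 per cell in four cells, so n = 70 per side for each main effect. SD 8.5. Significance level 0.05, taken as two-sided (tested below). Unadjusted comparison of post-treatment means. Drop-out is already removed from the 140.

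**Step 1: reproduce the 80% figure.** The normal approximation is d = (z_alpha + z_power) × √(2/n).
- √(2/70) = 0.1690.
- 80%: (1.960 + 0.842) × 0.1690 = 0.474 SD.
- Noncentral t with 138 df: 0.477 SD, which is the stated value. In points, 0.477 × 8.5 = 4.05.

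**Step 2: same method at 90%.**
- Normal: (1.960 + 1.282) × 0.1690 = 0.548 SD, or 0.548 × 8.5 = 4.66 points.
- Noncentral t: 0.552 SD, or 0.552 × 8.5 = 4.69 points.
- Stated: 0.522 SD, 4.4 points.
- Using the factorial model's residual degrees of freedom (136) leaves 0.477 and 0.552 unchanged to three decimals.

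**Step 3: a check that does not depend on n or SD.** The ratio of the two detectable effects is approximately (1.960 + 1.282)/(1.960 + 0.842) = 1.157. Then 0.477 × 1.157 = 0.552. The stated ratio is 0.522/0.477 = 1.094.

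**Step 4: power at the stated effect.**
- Normal: 0.522/0.1690 = 3.088; 3.088 − 1.960 = 1.128; power 87.0%.
- Noncentral t: 86.6%.

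**Step 5: sample needed for 90% at 0.522 SD.**
- Normal: 2 × (3.242/0.522)² = 77.1, so 78 per side.
- Noncentral t: 78.1, so 79 per side, or 158 analysed against 140.

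**Step 6: other readings of the inputs.**

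| Reading | Effect at 80% power | Effect at 90% power | Power at 0.522 SD |
|---|---|---|---|
| Stated | 0.477 | 0.522 | 90% |
| Two-sided 0.05, 70 v 70 | 0.477 | 0.552 | 86.6% |
| One-sided 0.05, 70 v 70 | 0.422 | 0.497 | 92.3% |
| Two-sided 0.05, 35 v 35 | not computed | not computed | 57.6% |

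The computed rows use the noncentral t. Of the readings tried, only two-sided 0.05 with 70 v 70 returns 0.477 at 80%, and none returns 0.522 at 90%.

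**The case against.** The other side has good points, and most of them limit how far this should be taken.

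- **Nothing in the design rests on 0.522.** The 80% figure is right, and the 140 analysed and 200 randomised are consistent with it. Recruitment stopped in June 2012 according to Trial status, so no decision about numbers remains open. This stands.
- **It is one error, not two.** 0.522 differs from 0.552 by a single digit, and the 4.4 points is that number multiplied by 8.5. This stands as the likeliest explanation, though the document does not confirm it.
- **Baseline adjustment may supply the missing power.** The article gives no baseline-to-outcome correlation r, so it has to be assumed. Power at 0.522 SD would be about 89.5% at r = 0.3, 91.7% at r = 0.4 and 94.3% at r = 0.5, with 90% reached from r of about 0.32 (1 − r² = 70/78.1 = 0.896). The adjusted analysis could therefore plausibly have the claimed power. That does not make the stated figure correct, because the stated calculation is unadjusted.

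A reader might go further and infer three things that the document does not support.

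- **That the abstract is false.** Power at 0.50 SD is 83.6%, but 0.50 is an outside convention. The abstract gives no number for a moderate effect, and 0.552 SD can be read as one.
- **That the calculation should not be called conservative.** The remark is explained by the next sentence: it refers to leaving out the hoped-for gain from baseline adjustment. It is defensible in that sense, whatever the digit.
- **That the trial is underpowered.** The article fixes no minimum important difference at 4.4 points, and the shortfall at 0.522 SD is only a few percentage points.

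**Conclusion.** The point holds as a correction to one stated figure. The paired statement of 0.522 SD and 90% power cannot be obtained from the section's own inputs, and the error is 0.552 − 0.522 = 0.03 SD, or 0.03 × 8.5 = about 0.25 points on a 0 to 40 scale. Expressed as power, it is 90 − 86.6 = 3.4 percentage points.

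The conclusion rests on a two-sided test, which is inferred from the 80% figure rather than stated, on equal halves of 70, and on an unadjusted comparison as the section describes. It does not depend on the SD of 8.5 except for the conversion to points. The importance is modest: the figure matters because it concerns the primary outcome and the power level quoted in the abstract, but the sample size, the planned analysis and the 80% statement are unaffected.

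**What to change.** In the Sample size section, replace 0.522 (about 4.4 points) with 0.552 (about 4.7 points) at 90% power. Alternatively, keep 0.522 SD and state its power as about 87%. Adding that the test is two-sided would let a reader reproduce both figures.

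For consistency, put 0.552 SD beside the 90% claim in the abstract, or make clear that this is the effect meant.

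Leave the 80% figure, the 140 and 200 patient targets and the remark about conservatism as they are. The cost is a small edit in two places and a slightly less favourable stated figure; no extra patients are needed.

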### Statistical analysis

Descriptive statistics will summarise demographic and clinical features of those referred, those randomised, those who complete the intervention (at least 5 cCBT sessions) and those who complete at least one set of post-baseline outcome measures. The same variables and baseline values of the outcome measures will be compared between brief and extended support, and between clinician and assistant at baseline. Where large differences exist, these variables will be included as potential confounders. Our primary analysis will be based on the first batch of completed postal questionnaires returned by the patients. These are posted out to the patients at 12 weeks post-randomisation but the timing of receiving completed questionnaires from the patients is variable. The time of receipt is recorded and may be included as a covariate.

Linear models will be used to estimate the main effects of the two treatments. An estimate and confidence interval for the interaction term will be obtained. Corresponding adjusted estimates will be obtained adjusting for baseline only, and for baseline and the potential confounders identified at baseline. Effect sizes will be calculated using Cohen’s d
[49]. The number of patients showing clinically significant and reliable change
[50] will be reported where possible. C-PAS and T-PAS will be compared for each group using mixed-effects models and their similarity will be assessed using intra-class correlation.

The primary analysis will include patients in the groups to which they had been randomly assigned regardless of the actual treatment they have received. The primary analysis will include non-missing data only, but the baseline characteristics of missing and non-missing values will be compared to assess the pattern of missing data. Further, as recommended by Altman
[51], sensitivity analyses will be performed by employing multiple imputation techniques. Where a few items within a scale are missing for an individual participant we will impute using that person’s scale average.

A per-protocol analysis will also be performed on the main outcomes using completers only, which we define as those patients who complete at least 5 cCBT sessions. We will compare sub-group effects by including interaction terms in appropriate linear models. We will use linear models to investigate which demographic and clinical variables predict primary outcome, session completion and patient satisfaction. Interaction terms may be included to investigate which variables modify the main effects. Secondary analysis will be carried out using the electronic data collected by the cCBT system in every session. The series of session electronic outcomes will be summarised and compared between treatment groups using repeated measures analysis.

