### Treatment allocation

Patients eligible for trial entry receive a treatment consent form and a set of blank standardised self-report questionnaires (baseline assessments) to complete and post to the research team in a stamped addressed envelope. On receiving the completed treatment consent form and baseline assessments, the research associate (JM) randomises patients into one of the four study intervention groups using a web-based system set up by the Clinical Research Trials Unit (CRTU) of the Norfolk & Norwich University Hospitals (NNUH) Trust. The system follows a block-randomisation: for every 32 referrals, it ensures that eight patients are assigned to each of the four arms of the trial so that the clinician and assistant who offer phone support to patients have similar workload distribution over time. Figure
1 is a CONSORT diagram
[31] of the randomisation and flow of participants through the study. 

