### Data collection

Baseline demographic and clinical characteristics are obtained by the self-referral questionnaire which is completed by patients and posted to the research team before randomization. The self-referral questionnaire has been suitably adapted for the purpose of this study from its previous validated version
[33]. The questionnaire has nine sections which elicit quantitative and narrative data about patients’ symptoms, computer literacy, lifestyle, past and present treatments including medication, and therapy goals and preferences for therapist-delivered interventions vs. computerised self-help.

Data on clinical outcomes, resource use and patient experiences are collected in two ways: both by post and electronically. Postal questionnaires are sent to patients at baseline (randomization) and then at weeks 12 (primary end-point) and 24 (follow-up) post-randomization with instructions to complete them and return to the research team. Electronic data are collected automatically by the cCBT system during each cCBT session. The timing of electronic data collection is recorded by the cCBT system but it varies according to the frequency with which patients log into it.

Narrative data are also collected during a 15 to 30 minute assessment with the patient pre-randomization, as part of support sessions by the clinician and the assistant, and during a 15 minute telephone interview, which asks about patient views and experiences of using a computerised self-help system and of having telephone support at 12-weeks post-randomization, by the study’s research associate (JM).

Below we give a detailed description of individual data collection tools and justification for their inclusion in the study. All standardised measures are self-reported and are collected independently of the staff proving telephone support; there are no observer-rated outcomes so there is no need for blinding.

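### Extra covariates for the fully adjusted estimate are chosen by chance baseline imbalance, not prognostic value, which gives up precision in that estimate

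*Protocol article*

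**What the plan says.** Under Statistical analysis, demographic and clinical variables and the baseline outcome values "will be compared between brief and extended support, and between clinician and assistant at baseline". The rule follows: "Where large differences exist, these variables will be included as potential confounders". No link with outcome is required.

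The same section plans linear models for the two main effects, then adjusted estimates "adjusting for baseline only, and for baseline and the potential confounders identified at baseline". That makes three estimates per main effect: unadjusted, baseline-adjusted, and baseline plus the selected variables. Only the third uses the rule. The article does not say which of the three is primary.

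The pool of candidates is wide. Under Data collection, the self-referral form is described thus: "The questionnaire has nine sections which elicit quantitative and narrative data". The baseline scales come on top of it. Under Treatment allocation, baseline assessments are returned before randomisation, and the blocked system works so that "for every 32 referrals, it ensures that eight patients are assigned to each of the four arms of the trial". No stratification by patient characteristics is described.

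The section also leaves one further covariate open ("The time of receipt is recorded and may be included as a covariate"). That is a separate choice and is not part of this point.

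**The concern.** Baseline variables are measured before a random allocation, so any difference between all the patients randomised to each level of a factor is a chance difference. Its size carries no information about whether the variable predicts 12-week WSAS, and prediction of outcome is what makes a covariate worth including.

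A rule based on imbalance therefore errs in two ways. It admits variables that do nothing for the estimate, and it leaves out strong predictors that happen to balance, although adjusting for those would still reduce the standard error. The content of the third model also depends on the draw of the randomisation and on what counts as large. The nominal standard error takes no account of the selection step. If the third estimate became the headline result, the trial would be reporting its least well-founded adjusted model.

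**Working it through.** **Inputs from the Sample size section.** "assuming a significance level of 0.05 with a standard deviation of 8.5 for that measure". "A sample size of 35 per group (total 140 patients) is sufficient to detect main effects", which gives 70 v 70 for each main effect. The effect at 80% power is 0.477 SD. Dropout is 30%, with 200 randomised (100 v 100 per factor).

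**Assumed, because the article does not give them:** the cut-off for a large difference, the number of variables screened (and their independence in step 3), and the covariate-outcome correlation. Ranges are shown.

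**1. The plan's own figures.** 0.477 × 8.5 = 4.05 points. At 70 v 70 and two-sided 0.05, 0.477 SD gives 80.6% power (normal) or 80.0% (t). 140 / (1 − 0.30) = 200. These reproduce and are used below.

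**2. Chance of a flag.** The standardised mean difference (SMD) of a baseline variable has SD sqrt(2/n) under randomisation: 0.141 for n = 100 per side and 0.169 for n = 70. So P(|SMD| > c) = 2 × (1 − Φ(c / sqrt(2/n))). With 20 variables and two factors there are 40 comparisons.

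| Cut-off c | P per variable, 100 v 100 | Expected flags, 100 v 100 | Expected flags, 70 v 70 |
|---|---|---|---|
| 0.2 | 15.7% | 6.3 | 9.5 |
| 0.3 | 3.4% | 1.4 | 3.0 |
| 0.4 | 0.5% | 0.2 | 0.7 |
| 0.5 | 0.04% | 0.02 | 0.12 |

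The comparison is made at baseline, so the 100 v 100 columns are the relevant ones.

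**3. Chance of at least one flag.** With 10 independent variables and two factors at 100 v 100, 1 − (1 − P)^20 is 97%, 80%, 50% and 9% at cut-offs 0.2, 0.25, 0.3 and 0.4.

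**4. Effect on the estimate.** The simulation used 20,000 runs at 70 v 70, with one standard normal covariate of correlation ρ with outcome. It was either ignored, always adjusted for, or adjusted for only when |SMD| > 0.25.

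| ρ | Selected by the rule | Power: ignored | Power: named in advance | Power: imbalance rule | Type I error: named in advance | Type I error: imbalance rule |
|---|---|---|---|---|---|---|
| 0 | 13.9% | 80.1% | 79.9% | 80.0% | 4.7% | 4.8% |
| 0.3 | 13.6% | 79.7% | 83.0% | 80.4% | 5.0% | 4.5% |
| 0.5 | 13.3% | 80.2% | 89.6% | 82.5% | 4.9% | 4.0% |
| 0.6 | 14.0% | 80.4% | 93.8% | 83.8% | 4.7% | 3.1% |

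The selection rate is about 14% at every ρ, so the rule does not distinguish useless variables from useful ones. At ρ = 0.5 the SD of the estimate was 0.168 ignored, 0.157 under the rule and 0.146 named in advance. The last agrees with sqrt(1 − 0.5²) × sqrt(2/70) = 0.146.

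The test becomes conservative because an omitted covariate is, by the rule, close to balanced. The estimate then varies less than the unadjusted standard error implies.

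**5. Limit of the illustration.** The simulation has no baseline WSAS term. In the third model the baseline value is already present, so ρ should be read as the correlation left after baseline adjustment, and the effect as a multiple of the remaining SD. For many variables that correlation will be lower than the raw one, and the loss smaller.

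**The case against.** The strongest reply is that little hangs on the rule. It touches one of three estimates. The baseline outcome value is a fixed covariate in both adjusted models, and the Sample size section names it as the hoped-for source of precision. In the simulation, power under the rule never fell materially below the unadjusted figure of about 80%, which is what the design promises. All of this stands, and it confines the point to the third estimate.

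Several stronger readings are tempting but unsupported:

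- **Inflated false positives.** A reader might infer this from a standard error that ignores selection. The simulated error goes the other way (4.5%, 4.0% and 3.1% at ρ = 0.3, 0.5 and 0.6).
- **Different models for the two factors.** Baseline values are compared by each factor, but the text speaks of one set of confounders, and one model with a pooled set is at least as natural a reading.
- **Many chance flags.** Six or more needs both 20 variables and a cut-off of 0.2. The abstract calls the design target moderate, and the Sample size section puts it at 0.477 to 0.522 SD. On that usage a large difference lies well above 0.2, and the expected number of flags can be close to zero. The 70 v 70 counts also describe the analysed subset after attrition, where differences need not be pure chance.
- **The missing threshold as a fault in itself.** An article may leave that to the analysis plan. Defining it would not cure the problem, since a precise imbalance rule still ignores prognosis.

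The reply does not rescue the rule. The article states it outright, and it is a poor way to choose covariates at any threshold.

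**Conclusion.** The point holds for the third, fully adjusted estimate only. The rule selects covariates on chance imbalance and forgoes most of the precision that prognostic variables other than the baseline outcome could add. Under the stated assumptions (70 v 70, 0.477 SD, one covariate, cut-off 0.25), the shortfall against naming the covariate in advance is about 3 points of power at ρ = 0.3 (83.0% v 80.4%), 7 at 0.5 (89.6% v 82.5%) and 10 at 0.6 (93.8% v 83.8%), with a mildly conservative test. The number of variables flagged cannot be settled from the article: 6.3 to 0.02 over cut-offs 0.2 to 0.5 with 20 variables at 100 v 100.

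The unadjusted and baseline-only estimates are sound on this point, and the documents do not support a claim that the trial's main result is compromised. The matter would weigh more if the third estimate were taken as primary, which the article leaves open. It is worth correcting because the better method is simple and nearly free.

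**What to change.** Replace the sentence with a short list of covariates chosen for expected prognostic value from variables already collected, and fix it before outcome data are examined. Candidates include baseline depression severity, concurrent treatment and referral source; the final choice is the sponsor's. Add the list to the baseline outcome value and fit one model containing both factors. Keep the baseline tables descriptive and do not use them to select covariates. State which estimate is primary: either the baseline-adjusted one or the one with the pre-specified list.

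The cost is a sentence or two in the analysis plan, with no new data and no change to the sample size. The Trial status section reports that data collection was still to continue after recruitment stopped, so the list could be fixed before outcomes are analysed.

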#### Telephone support

Individual support is given as a scheduled, telephone call on average once a week or fortnight (depending on how fast the patient goes through the programme) for 3 months or longer, and up to 6 months if needed. Support sessions are either brief (5 to 10 minutes per call) or extended (20 to 30 minutes per call). Patients can receive up to 12 telephone calls over 12 to 24 weeks, so they have a maximum of 1 to 2 hrs of brief support or 4 to 6 hrs of extended support throughout using the cCBT system. *Ad-hoc* contact is also available, in case patients raise risk issues or get stuck with the system.

Both brief and extended support sessions focus on monitoring patient progress and mental state as necessary. Extended support sessions offer additional therapy advice by elaborating on some of the treatment techniques described in the cCBT system (for example, to help patients identify thinking errors and alternative beliefs, problem-solving difficulties with doing homework, etcetera). Support is not standardised, so that it can be tailored to individual patients’ needs and preferences.

Support sessions are offered either by a clinician (JT), a PhD nurse with CBT clinical qualifications and 20 years clinical experience, or by an assistant (KB), a graduate psychologist with no clinical qualifications but with 2 years experience of working with people with depression and anxiety in a voluntary organisation. Both members of staff receive individual telephone or face-to-face clinical supervision from a senior CBT-trained Clinical Psychologist (NR) and research supervision from the Chief Investigator (LG).

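### Time of questionnaire receipt, a post-randomisation variable, is allowed as a covariate in the analysis of the 12-week primary outcome and can bias the main effects

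*Protocol article*

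**What the plan says.** All of this is in the protocol article.

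- **Endpoint.** Data collection places the postal outcomes at "weeks 12 (primary end-point) and 24 (follow-up) post-randomization".
- **Data for the primary analysis.** Statistical analysis states: "Our primary analysis will be based on the first batch of completed postal questionnaires returned by the patients". It explains that the forms go out at week 12 but that "the timing of receiving completed questionnaires from the patients is variable".
- **The covariate.** The next sentence is "The time of receipt is recorded and may be included as a covariate". No condition for using it is given.
- **The models.** The next paragraph describes linear models for the two main effects, an interaction estimate, and further estimates "adjusting for baseline only, and for baseline and the potential confounders identified at baseline". Receipt time is in neither adjustment set.
- **Population.** Patients are analysed in the groups to which they were randomised, and "The primary analysis will include non-missing data only".

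**The concern.** A covariate is safe in a randomised comparison when it is fixed before allocation. Receipt time is not. It is observed at or after week 12, when patients have had about three months of the support being compared.

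The protocol itself gives reason to think that receipt time could be linked to both arm and outcome:

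- **Arm to receipt time.** The third primary objective compares attrition, usage and experience between support types, and the Background asks whether longer sessions might improve completion. The trial therefore treats engagement as something support may change. Prompt return of a form is one aspect of engagement.
- **Receipt time to outcome.** The Discussion says that depression impairs motivation. Patients who return forms slowly may therefore also be those with poorer functioning.

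If both links hold, comparing arms at equal receipt time compares patients who differ in motivation, although randomisation had balanced it. If delay itself changes the score, adjustment removes part of the total effect. In either case the estimate no longer answers the randomised question cleanly.

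**Working it through.** **The design figures, reproduced**

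Inputs from Sample size: SD 8.5, alpha 0.05 (taken as two-sided), 35 per cell, hence 70 vs 70 for each main effect.

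- Target: 0.477 × 8.5 = 4.05, stated as about 4.1 points.
- Power at 0.477 SD with 70 vs 70: 80.6% (normal) or 80.0% (noncentral t), as stated.
- Randomised: 140 / (1 − 0.30) = 200, as stated.
- Standard error of a main effect before covariates: 8.5 × √(2/70) = 1.44 points.

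**How adding receipt time moves the arm estimate**

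Let R be receipt time in within-arm SD units, *a* the arm's effect on R, and λ the coefficient of R in the model with arm. Then

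adjusted arm effect − unadjusted arm effect = −a × λ.

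The shift vanishes if either factor is zero.

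**Illustrative sizes**

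The protocol gives no value for *a* or λ, so everything here is assumed:

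- U is an unmeasured patient state (higher is worse), with variance 1.
- R = a·arm + g·U + error, with within-arm variance 1.
- Outcome in SD units = √0.5·U + s·R + error, with error variance 0.5 and no direct arm effect.
- Hence λ = g × 0.707 + s, and the shift in points is −a × λ × 8.5.

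| a | g | s | −a × λ (SD) | Shift (WSAS points) |
|---|---|---|---|---|
| 0 | 0.3 | 0 | 0 | 0 |
| 0.3 | 0 | 0 | 0 | 0 |
| 0.3 | 0.3 | 0 | −0.3 × 0.212 = −0.064 | −0.54 |
| 0.5 | 0.3 | 0 | −0.5 × 0.212 = −0.106 | −0.90 |
| 0.5 | 0.5 | 0 | −0.5 × 0.354 = −0.177 | −1.50 |
| −0.5 | 0.3 | 0 | +0.5 × 0.212 = +0.106 | +0.90 |
| 0.3 | 0 | −0.2 | +0.3 × 0.2 = +0.060 | +0.51 |

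Simulation with 2 million patients per row gives the same shifts. In the first six rows the model without R is unbiased at zero. In the last row the arm has a true total effect of 0.3 × (−0.2) = −0.06 SD through delay, and adding R removes it.

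Lower WSAS is better. An arm that slows return is therefore made to look better (negative shift), and one that speeds return is made to look worse.

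**Effect of adjusting for baseline WSAS as well**

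Assume that baseline correlates 0.7 with U and is otherwise unrelated to R. The variance of U given baseline is 1 − 0.49 = 0.51.

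- a = 0.5, g = 0.5: λ = (0.354 × 0.51) / (0.25 × 0.51 + 0.75) = 0.180 / 0.878 = 0.205. The shift is 0.5 × 0.205 × 8.5 = 0.87 points in size, down from 1.50.
- a = 0.3, g = 0.3: λ = (0.212 × 0.51) / (0.09 × 0.51 + 0.91) = 0.108 / 0.956 = 0.113. The shift is 0.3 × 0.113 × 8.5 = 0.29 points in size, down from 0.54.

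Baseline adjustment reduces the bias but does not remove it.

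**The case against.** The strongest reply is that the article commits to nothing. The wording is permissive, the adjusted models that it lists use only baseline information, and patients stay in their randomised groups. Estimates without receipt time are planned in any case. This stands, and it limits the point to a possible extra adjustment.

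Second, the link from arm to receipt time is not demonstrated. Outcome forms come by post and are gathered independently of the support staff. The ceiling on calls is common to all arms ("Patients can receive up to 12 telephone calls over 12 to 24 weeks"), so the randomised factors are call length and type of supporter, not the number of calls offered. This also stands. It makes the link uncertain but does not exclude it, and the objectives treat engagement as open to influence.

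Third, there is a reasonable motive: return times do vary, and a covariate can look like the natural correction. But a covariate that treatment may affect is not a safe correction.

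A reader might infer three stronger things that the document does not support:

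- **That a form returned at any date counts as the 12-week outcome.** The article says only that timing varies. A return limit is a detail that a condensed article may leave to the full protocol or analysis plan. Support may continue "for 3 months or longer, and up to 6 months if needed" in every arm, so it can still be running for a form returned exactly on time.
- **That the covariate will be chosen once results are known.** The permissive wording fits equally well with a decision made in the analysis plan before unblinding.
- **That the primary estimate is no longer a randomised comparison.** That would follow only if the term were used and both links existed.

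**Conclusion.** The point holds in a limited form. The article allows a post-randomisation variable into the analysis of its primary outcome, and if that option is used the main-effect estimates can be biased in either direction.

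The size cannot be found from the document. Under the assumed relations it runs from 0 to about 1.5 WSAS points. The upper end is 1.5 / 4.1 = 37% of the target difference and about one standard error (1.5 / 1.44 = 1.04). Adjusting for baseline WSAS would probably lower these figures. The bias is exactly zero if the arm does not affect receipt time, or if receipt time is unrelated to outcome within arms. These figures show that the risk is not negligible; they are not an estimate of bias in this trial.

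**What to change.** State in Statistical analysis that time of receipt will not be a covariate in the primary model, which adjusts only for baseline variables. Report receipt time by arm descriptively. Show any model that includes it only as a labelled sensitivity analysis.

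Setting late forms to missing is not a substitute. It selects patients on the same post-randomisation variable and, because the primary analysis uses non-missing data only, would drop them from it.

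The cost is one sentence. The 140 analysed, the 200 randomised and all stated effect sizes are unchanged. What is given up is a small possible gain in precision. If the arm did not affect receipt time, and without baseline adjustment, including it would cut the standard error by 1 − √(1 − 0.212²) = 2% at g = 0.3, or 1 − √(1 − 0.354²) = 6% at g = 0.5. The planned baseline adjustment offers a gain in precision without the same risk.
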